#### Nursing evaluation

2.4.3

The evaluation will be performed at the nursing station at Ace and includes the collection of anthropometric data such as weight, height, abdominal circumference, and blood pressure, providing key indicators of participants’ physical health. Blood samples are collected for genetic analyses at baseline and for metabolic and proteomic studies at both baseline and follow-up assessments. Additionally, the study incorporates validated tools to assess health risks and comorbidities. Together, these measures ensure a comprehensive evaluation of participants’ biological and physical health profiles, supporting the exploration of potential associations between these factors and cognitive decline.

#### MRI acquisition and preprocessing

2.4.4

A Siemens MAGNETOM VIDA 3T scanner (Erlangen, Germany) equipped with a 32-channel head coil will be utilised at Clínica Corachan facilities in Barcelona. Anatomical images for volumetric analyses will be acquired using a T1-weighted 3D MPRAGE sequence, providing high-resolution structural data. Diffusion tensor imaging will be performed using an EPI sequence with 64 diffusion directions to assess white matter integrity. Additional sequences will be employed to detect ischemic damage and microbleeds, enabling a comprehensive evaluation of vascular contributions to cognitive impairment. All acquired images will be processed and analysed at the Neuroimaging Lab at Ace, ensuring consistency and quality in image interpretation and data extraction.

#### Fluid biomarkers acquisition and measurements

2.4.5

Several biospecimen samples are collected on the same day, forming part of the biobank at Ace, which is officially registered with Instituto de Salud Carlos III (code C.0000299). Ace's samples collection protocols have been approved by the Clinical Research Ethics Commission of the Hospital Clinic (Barcelona, Spain, reference num: HCB/2014/0494) in accordance with the Declaration of Helsinki and the current Spanish regulations in the field of biomedical research (law 14/2007, royal decree 1716/2011).

Blood samples are collected in polypropylene tubes with EDTA (BD Vacutainer). Plasma is separated by centrifugation, aliquoted, and stored at −80°C until use. CSF is obtained through lumbar puncture, performed by an experienced neurologist at Ace following established consensus recommendations. The procedure is carried out on fasting patients, who are seated and locally anesthetised with 1% subcutaneous mepivacaine. A total of 13 mL of CSF is collected using polypropylene tubes (Sarstedt Ref 62.610.018). CSF samples are centrifuged (2,000× g, 10 min, 4°C). The resulting supernatant is divided into aliquots and stored at −80°C for subsequent analyses. This collection protocol strictly adheres to the recommendations outlined by the Alzheimer's Biomarker Standardization Initiative (40), ensuring high-quality and standardised sample handling for biomarker evaluation. AT(N) classification will utilise core CSF biomarkers, including amyloid-β40 (Aβ40), amyloid-β42 (Aβ42), phosphorylated tau (pTau181), and total tau (tTau). Positivity thresholds follow the cut-offs established by the CSF program at Ace Alzheimer Center Barcelona (41), these cut-off values are based on validated population-derived distributions and have been previously applied in clinical and research cohorts to characterize neurodegenerative progression. In addition, plasma biomarkers (pTau217) are measured for research purposes (42).

#### Genotyping

2.4.6

Genomic DNA is extracted from buffy coat samples using the Maxwell RSC 48 instrument (Promega) with the AS1540 DNA extraction kit, ensuring high-quality samples for genetic analysis, and targeting genotype variants included in the latest Polygenic Risk Score (PRS) for AD, including *APOE*. *APOE* genotypes are determined using fluorogenic allele-specific oligonucleotide probes via the TaqMan assay (Life Technologies, Spain) for the *APOE* genetic variants rs7412 (Test ID: C_904973_10) and rs429358 (Test ID: C_3084793_20). For the TaqMan assays, polymerase chain reaction (PCR) and real-time fluorescence measurements are performed on the QuantStudio3 real-time PCR system (Thermo Fisher Scientific, Spain) utilizing the TaqMan Universal Master Mix system (Ref: 4364341, Life Technologies, Spain), strictly following the manufacturer's protocol. The PCR protocol consists of an initial read step at 60°C for 30 s, followed by 40 cycles comprising an initial denaturation at 95°C for 10 min, a denaturation step at 95°C for 15 s, and annealing at 60°C for 1 min. The process concludes with a final post-read step at 60°C for 30 s. Genotypes are determined through the Genotyping application available on Thermo Fisher Cloud, employing cluster analysis to ensure accurate identification. This standardised methodology provides reliable *APOE* genotyping for downstream analyses. Additionally, DNA from the same participants is sent for genotyping using the Axiom 815K Spanish biobank array (according to the manufacturer's instructions—Axiom™ 2.0 Assay Manual Workflow, Thermo Fisher) at the Spanish National Center for Genotyping (CeGEN, Santiago de Compostela, Spain). Details on genotyping and quality control procedures are provided elsewhere (43). PRS were calculated following (44), using a list of 83 single nucleotide polymorphisms.

#### Spontaneous speech

2.4.7

The evaluation of spontaneous speech is an integral part of the assessment protocol provided by Punto Health (45). Ace has extensive experience in administering and processing of spontaneous speech protocols, as demonstrated in recent publications from our group (23, 24).

This assessment is designed to be conducted exclusively in a remote setting, such as the participant's home, ensuring convenience and minimizing disruptions to daily life. The protocol is administered via a mobile application that is downloaded onto the participant's or caregiver's device. The speech assessment involves a picture description task where they describe a given image for one minute, followed by a semantic category fluency task, listing as many items as possible within a given category, such as fruits or professions, within a minute. Finally, open-ended questions prompt participants to describe personal experiences and daily routines. All three tasks are completed within 3 minutes.

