#### Translational objectives

2.2.2

Patient well-being and intervention impact: To examine the intervention's effects on participants’ physical, psychological, social, and functional well-being, providing a holistic understanding of health, lifestyle, and care needs.Biological and cognitive interactions: To investigate the relationship between biological markers, including genetic profiles, CSF and plasma biomarkers, and MRI measures, and cognitive decline, and to identify the conditions under which e-health interventions are most effective. Plasma biomarkers will be measured at baseline, year 1, and year 2 to track longitudinal changes.Spontaneous speech analysis: To employ automated speech processing for analysing spontaneous speech as a remote and scalable proxy for cognitive status, complementing traditional neuropsychological assessments (23, 24).AI platform development: To contribute to the generation of multidimensional datasets that integrate clinical, biological, cognitive, and patient-reported outcomes in order to refine and validate the VHP's AI models, and to characterize the intervention's efficacy across diverse metrics for the benefit of participants and caregivers.

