#### Neuropsychological assessment

2.4.2

The NBACE is a comprehensive tool designed to assess multiple cognitive, emotional, and functional domains. Table 2 provides an overview of all domains and their corresponding tests, offering a clear and concise summary of the full assessment structure. This table serves as the primary reference for the components included in the NBACE.

**Table 2 T2:** Neuropsychological battery used in Ace (NBACE), assessment structure across cognitive and functional domains.

Category	Measurement tool/description
Reality orientation	Temporal, spatial and personal orientation tests
Attention & working memory	Digital Forward subtest of the Wechsler Adult Intelligence Scale, Third Edition (WAIS-III) (73)
Verbal learning & memory	Word List subtest from the Wechsler Memory Scale, Third Edition (WMS-III) (74)
Language	Abbreviated Boston Naming Test (15-BNT) (75)
	Sentence repetition
	Verbal comprehension of commands (simple, semi-complex, complex)
	Phonetic and semantic verbal fluency tasks (76)
Visual gnosis	Poppelreuter-type Overlap Figures (77)
	Lurias Clocks test (78)
	The 15-Object test (79)
Motor praxis	Imitation and ideomotor praxis tasks
	WAIS-III Block Design subtest (73)
Executive functions	Automatic Inhibition subset of the Kurtz Syndrome Test (SKT) (80)
	Similarities and Digit backward subtest of WAIS-III (73)
	Clock Drawing Test (81)
Mood	Hospital Anxiety and Depression Scale (HADS) (82)
Functional abilities	Activities of Daily Living (ADL) (83)
	Instrumental Activities of Daily Living (IADL) (84)
Quality of life	Quality of Life in Alzheimers Disease (QoL-AD) (85)

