Healthentia (46). Healthentia is a class IIa medical device, intended for supporting subject telemonitoring, decision-making and virtual coaching (47, 48). The collection of physiological data includes heart rate, blood pressure, oxygen saturation, and weight, directly transmitted to care providers via automated electronic means in combination with validated internet of things devices (when available for other clinical partners, not for our pilot). The information collected is further enriched with the transmission of patient's outcomes and outcome scores related to patient's health status, health-affecting factors, health-related quality of life, disease knowledge and adherence to treatment, through validated questionnaires. Participants capable of remotely interacting with the tool beyond face-to-face sessions tend to report more frequently, contributing regular (daily or weekly) data that can inform timely care plan adjustments. All these parameters are visualised (subjects-based dashboards) and mathematically treated (trends analysis, alerts) for supporting experts’ decision-making procedures.Eligence (49). Eligence is an online platform designed for brain training through interactive games, created by specialists in neuropsychology aimed at individuals in the early stages of dementia, for rehabilitation and prevention of cognitive decline. It features 40+ games and activities that exercise the basic cognitive skills such as memory, reasoning, attention, orientation, executive functions, construction skills, language. Through Eligence, healthcare professionals can create personalised training sessions for individuals and groups, monitor performance in real-time and easily generate detailed evaluation reports. It is accessible from anywhere and any device with an internet connection.Linguistic Games (50). A novel cognitive and linguistic tool has been designed upon the main objective to exploit multiple cognitive processes that are involved in language performance and speech production and comprehension. The initial functionality of the mock-up tool was in 2D, but also some subtasks have been designed in 3D to introduce higher cognitive-processing demands; however, the tool is not intended as different versions for separate groups but rather as graded levels of difficulty applicable across healthy adults, adults with subjective cognitive decline, and those with mild cognitive impairment. These novel linguistic tests can assess different cognitive abilities through the vehicle of language competence such as attention, memory, language, psychomotor abilities, processing speed and executive functions. The linguistic mock-up has been designed based on Usability and Accessibility Guidelines (51–55), while realistic contexts from older adults’ daily routines have been incorporated for example tasks based on vocabulary or short scenarios related to household chores, daily mobility, travel planning or participation in social events (56).The data generated by these three digital tools, as well as the clinical, neuropsychological, or biological data relevant to the project—whether retrospective (historical data from Ace) or prospective (related to the follow-up of the two study groups)—will be shared with the Consortium using the VHP. These multimodal data will feed into the platform and serve as input for AI algorithms and PDTs, which aim to predict individual health trajectories and propose tailored interventions. This process exemplifies the integration of digital tools, clinical knowledge, and computational models into a unified, adaptive care system. Audio recordings from the spontaneous speech protocol will not be shared for confidentiality reasons.

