### Analysis plan

2.7

The primary objective of Pilot 3 is to compare cognitive decline between the active and control groups after a two-year follow-up period. The neuropsychological structure underlying the primary outcome has been previously defined and validated by an expert panel of neuropsychologists (26, 27). Based on this structure, five composite scores will be derived using Structural Equation Modelling, following the methodology described in (23). To evaluate the impact of the intervention across two conditions on these neuropsychological composites, mixed models will be employed. These models will include three time points (baseline, one-year follow-up and two-year follow-up) and will also be applied to secondary outcome measures, such as quality of life, physical activity, and satisfaction with the intervention. Alterations in plasma biomarkers, including pTau181 and pTau217, will adhere to the same analytical framework, allowing for a comprehensive evaluation of both cognitive and biological markers.

In addition, the study will explore modulating effects, such as biological factors (AD-related biomarkers in CSF, PRS, *APOE*, MRI parameters, plasma biomarkers, comorbidities, and medication use) through interaction analyses within the mixed models. Associations between spontaneous speech measures, neuropsychological composites, and plasma biomarkers will be examined using regression models and advanced machine learning techniques. This aspect of the study aims to identify the most predictive parameters of pre- and post-intervention slopes across the five neuropsychological composites. By leveraging these predictive models, the study seeks to advance the understanding of how specific variables contribute to cognitive decline and its modulation, ultimately informing precision medicine approaches for dementia care.

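### Semantic fluency sits in both the remote speech protocol and the NBACE, so the association with any composite containing it may overstate how well spontaneous speech tracks cognition

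*Protocol article*

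**What the plan says.** - **Aim.** Section 2.2.2 of the protocol article lists, as a translational objective, "analysing spontaneous speech as a remote and scalable proxy for cognitive status, complementing traditional neuropsychological assessments".
- **Predictor side.** Section 2.4.7 describes three remote tasks: a one-minute picture description, "followed by a semantic category fluency task, listing as many items as possible within a given category", also limited to a minute, and then open-ended questions about personal experience and routine.
- **Criterion side.** Section 2.4.2, Table 2, lists "Phonetic and semantic verbal fluency tasks" under Language. It does not give the semantic category or how the test is administered.
- **Composites.** Section 2.7 states that "five composite scores will be derived using Structural Equation Modelling" and refers to a cited method. It does not say which tests enter which composite.
- **Analysis.** Section 2.7 continues: "Associations between spontaneous speech measures, neuropsychological composites, and plasma biomarkers will be examined using regression models and advanced machine learning techniques". The planned features are acoustic, prosodic, temporal and linguistic, and the linguistic ones include measures related to fluency.
- **Arms.** Section 2.6 describes Linguistic Games, one of the three tools for the active arm, as designed to "exploit multiple cognitive processes that are involved in language performance and speech production and comprehension". The control arm does not use the platforms.

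**The concern.** To support the claim that spontaneous speech is a proxy for cognition, the speech measure has to predict something other than itself. Listing items from a category against the clock is a standard neuropsychological test, not spontaneous speech. If it feeds the speech features and also sits inside the composite being predicted, two administrations of one type of test share variance specific to that test. That variance counts as accuracy of the speech proxy, yet it says nothing about picture description or open-ended talk.

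What is at stake is the interpretation of one translational objective. A sponsor who wants to use speech remotely at scale could not tell whether the free-speech tasks carry the signal or whether a short fluency test would do as well.

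A second, smaller matter concerns the arms. Only the active arm spends a year with a tool built around language, so the relation between speech and cognition after the intervention may not be the same in both arms.

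**Working it through.** The article states no correlation, accuracy target or power for the speech analysis, so there is no figure to reproduce. Every numerical input in steps 1 to 3 is an assumption, except the three speech tasks (section 2.4.7) and the 50:50 allocation (section 2.3).

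**1. Overlap, three-task or fluency-only speech score**

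The composite is the mean of k tests, each loading a on a common factor. The speech score is the mean of m tasks, each loading b. The two fluency tasks also share a fraction s of their specific variance.

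- Covariance = ab + s√((1−a²)(1−b²))/(km). The second term is the overlap.
- Composite variance = a² + (1−a²)/k. Speech variance = b² + (1−b²)/m.
- r = covariance / √(product of the variances).

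Example with a = b = 0.5, s = 0.5, k = 5, m = 3:
- covariance = 0.25 + 0.5 × 0.75/15 = 0.275
- variances = 0.40 and 0.50, and √0.20 = 0.447
- r = 0.275/0.447 = 0.615 with the overlap term, and 0.25/0.447 = 0.559 without it.

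Selected settings with k = 5, each shown as r without → with the overlap term:

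| a | b | s | Three tasks | Fluency only (m = 1) |
|---|---|---|---|---|
| 0.5 | 0.3 | 0.7 | 0.378 → 0.475 | 0.237 → 0.420 |
| 0.5 | 0.5 | 0.5 | 0.559 → 0.615 | 0.395 → 0.514 |
| 0.7 | 0.3 | 0.5 | 0.435 → 0.482 | 0.273 → 0.361 |
| 0.7 | 0.5 | 0.3 | 0.643 → 0.666 | 0.455 → 0.503 |

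Over a = 0.5 or 0.7, b = 0.3 or 0.5 and s = 0.3 to 0.7, the overlap adds about 0.02 to 0.10 for the three-task score. For fluency-only features it adds about 0.05 to 0.18 against a five-test composite and 0.11 to 0.37 against a two-test composite. For a composite without semantic fluency the overlap term is zero.

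**2. The extreme case: a fluency score as sole predictor**

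Assume a composite of k equally weighted tests with mean inter-test correlation ρ, and a remote-to-clinic fluency correlation of 0.75.

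- With fluency in the composite: R² = [(0.75 + (k−1)ρ)/k]² / [(1 + (k−1)ρ)/k].
- With fluency removed: R² = ρ² / [(1 + (k−2)ρ)/(k−1)].
- k = 4, ρ = 0.4: 0.4875²/0.55 = 0.43, against 0.16/0.60 = 0.27.
- k = 6, ρ = 0.5: 0.5417²/0.5833 = 0.50, against 0.25/0.60 = 0.42.

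Between 62% (0.267/0.432) and 83% (0.417/0.503) of the R² survives removal.

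**3. Arm**

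Let r be the within-arm correlation, and let d₁ and d₂ be the training shifts, in SD, on speech and on the composite. With 50:50 allocation:

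- pooled r = (r + 0.25 d₁d₂) / √((1 + 0.25 d₁²)(1 + 0.25 d₂²)).
- r = 0.40, both shifted by 0.5: 0.4625/1.0625 = 0.435 (up).
- r = 0.40, only speech shifted by 0.5: 0.40/√1.0625 = 0.388 (down).

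For r from 0.2 to 0.6 and shifts from 0 to 0.5, the change runs from about −0.02 to +0.05. Baseline data are untouched.

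**The case against.** The strongest reply has four parts.

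- **Condensed article.** Feature sets by task and covariates for an exploratory analysis belong in the full protocol or SAP, which are not shown. This stands as far as the missing detail goes, and those documents may already deal with the matter. The overlap itself is not an omission, because the task content and battery content stated in the article create it.
- **Convergent validity.** A remote measure that shares a construct with the clinic test is ordinary evidence of validity. That is fair for a remote fluency test. It does not carry over to a claim about spontaneous speech.
- **Dilution.** Fluency is one of three tasks, and many planned features are acoustic or prosodic. This stands, and it is why the three-task figures are smaller than the fluency-only ones.
- **Existing safeguards.** Section 2.7 plans wrapper-based feature selection and SHAP. These may show that fluency features dominate, but neither gives the accuracy obtained without them. Selection for predictive performance may favour the overlapping feature.

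A reader might also infer stronger things that the documents do not support:

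- *A good result could come entirely from the shared test.* Step 2 shows that most of the R² survives removal even with fluency as sole predictor.
- *All speech associations are inflated.* Overlap can act only where semantic fluency enters the composite.
- *The identical task is used twice.* Only the task type is known to be shared.
- *Training the active arm inflates the association.* Step 3 shows no fixed direction.
- *The plan has chosen to pool the arms with no arm term.* The article is simply silent on how arm is handled in these models.

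**Conclusion.** The point holds in a limited form. For whichever NBACE composite contains semantic fluency, the planned association with speech partly reflects the same type of test on both sides. It may overstate how well picture description and open-ended speech track cognition. Language is the likely composite, but membership is not stated.

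The size cannot be fixed from the article. It rests on assumed loadings, on an assumed shared specific variance and on equal weights in place of the unstated structural-equation weights. On those terms it is about 0.02 to 0.10 in r for a three-task score and more for fluency-only features. The slope models were not evaluated.

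Composites without fluency, plasma biomarkers and the primary comparison between arms are unaffected. The arm question supports a secondary check only: the relation may differ by arm after the intervention, in either direction. This is a low-severity point with an inexpensive remedy.

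**What to change.** In section 2.7:

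1. Report speech associations and prediction accuracy separately for picture description, fluency and open-ended questions.
2. Repeat them with semantic fluency left out of the speech features or out of the composite, beside the full version. State in advance that the spontaneous-speech proxy claim rests on the non-overlapping version.
3. State which tests enter each composite, so that readers can see where the overlap applies.
4. As a secondary check, show the association at baseline and, after the intervention, by arm.

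One caution on reading the two versions: dropping a test also shortens the score. In the worked example, removing the overlap term alone takes r from 0.615 to 0.559. Dropping fluency from the composite (k = 4, variance 0.25 + 0.75/4 = 0.4375) gives 0.25/√(0.4375 × 0.50) = 0.535. Dropping it from the speech score (m = 2, variance 0.25 + 0.75/2 = 0.625) gives 0.25/√(0.40 × 0.625) = 0.500. The gap between versions should therefore not be read wholly as overlap.

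The cost is a few extra models on data already being collected, two versions of the result to present, and somewhat lower reported accuracy.
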